#### Qualitative interviews

All interview data will be analysed using thematic analysis [101], which results in a rich and accessible account of qualitative data. This process involves systematically and iteratively coding information from interviews under main headings and subcategories, and using previous literature to support the validity of categories. Member checking strategies [102] will be employed for this stage of the analysis with participants, members of the research team, and expert-by-experience consultants, to maximise the transparency and trustworthiness of the data. Data management and analysis will be supported by NVivo software. Analysis will occur in parallel with data generation and will continue until thematic saturation is achieved (the point at which no new categories emerge). All trial documentation and data will be retained for a minimum of 10 years, as stated in Clinical Trials Regulations.

### Interim analyses {21b}

No interim analyses are planned.

### Methods for additional analyses (e.g. subgroup analyses) {20b}

Any putative subgroups, including centre, will be assessed by including an interaction term between randomisation and the subgroup variable, as well as a main effect for the subgroup if not already in the model. All additional analyses will be clearly specified in the Statistical Analysis Plan and reviewed by the DMEC.

### Methods in analysis to handle protocol non-adherence and any statistical methods to handle missing data {20c}

The random effect structure of the main analyses will account for repeated measures and clustering due to the partial nested design. All models will be estimated using maximum likelihood estimation, which allows for missing outcome data under the Missing At Random assumption; we may also use inverse probability weighting to adjust for non-adherence to allocated treatment and other intermediate outcomes as predictors of future loss to follow-up. A dose-response model will be considered to estimate a linear effect of amount of therapy, with randomisation as an instrumental variable for the number of TF-CBT sessions attended. Complier-average causal effects will be estimated using instrumental variable methods or finite mixture models, using pre-specified definitions of compliance/fidelity in the TF-CBT arm.

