### Sample size {14}

We will recruit 300 people for the study, 150 in each group, and 60 per site.

Sample size calculations accounted for clustering in therapy arm with intraclass correlation (ICC) = 0.01 with 10 therapists over the trial period, each with an average of 12 participants and variation in the cluster size of 12; no clustering in TAU group; 1:1 allocation; 0.05 significance level; baseline-endpoint correlation of 0.5 (range in previous data [19, 25]: 0.4–0.7) reducing the standard deviation (SD) to 0.866 from a standardised value of 1.

Allowing for 20% attrition to primary endpoint, 120 people per group in the analysis set has 91% power to detect an effect size of 0.4. As a sensitivity check, with 240 participants in the analysis set, if the ICC = 0.05 we would still retain 85% power. Alternatively, if the ICC = 0.01, a sample size of 240 participants has 80% power to detect an effect size of 0.33.

For the qualitative study, we will recruit 35 participants (7 per site) and between 5 and 10 therapists (1–2 per site, depending on number of therapists employed per site). At least five participants (one per site) who chose to end therapy prematurely will be included in the interviews.

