## Statistical methods

### Statistical methods for primary and secondary outcomes {20a}

#### Primary and secondary outcomes

We will report data in line with the CONSORT-SPI [74] statement showing attrition rates and loss to follow-up. All analyses will be carried out using the intention to treat principle, incorporating data from all participants including those who do not complete therapy. Every effort will be made to follow up all participants in both arms for research assessments.

Analyses will be conducted in Stata version 15 or later. Descriptive statistics within each randomised group will be presented for baseline values. These will include counts and percentages for binary and categorical variables, and means and standard deviations, or medians with lower and upper quartiles, for continuous variables, along with minimum and maximum values and counts of missing values. There will be no tests of statistical significance or confidence intervals for differences between randomised groups on any baseline variable.

Treatment effects on primary and secondary outcomes will be estimated using linear mixed models. Fixed effects will be centre, baseline assessment for the outcome under investigation, group, time (categorical), and time × group interactions. Participant and therapist will be included as random intercepts. Marginal treatment effects will be estimated and reported for each time point as adjusted mean differences in scores between the groups with 95% confidence intervals and 2-sided *p*-values. For binary secondary outcomes, the same approach will be followed using logistic mixed models and effects will be reported as conditional odds ratios.

The analysis will be conducted in two separate stages. The primary analysis will estimate treatment effects at the primary endpoint of 9 m, using all outcome data from 4 and 9 months. Analysis will take place after the last participant has completed their 9 m assessment and will report the estimated effects at 4 and 9 months. The results will not be shared with the blinded assessors, nor outside of the STAR team, until all 24-m assessments have been completed, to avoid any biases on data collection.

The secondary analysis will estimate treatment effects at 24 m, using all outcomes from 4, 9, and 24 months. Analysis will take place after the last participant has completed their 24-m assessment, and will report the estimated effect at 24 m.

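### Fixing maximum likelihood for the primary mixed model, with about ten therapists, can put the nominal 5% test somewhat above 5%; REML serves the stated purpose equally well

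*Protocol article*

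**What the plan says.** The section on non-adherence and missing data {20c} sets one estimation rule for every model: "All models will be estimated using maximum likelihood estimation, which allows for missing outcome data under the Missing At Random assumption". No other reason for ML is given.

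Under Statistical methods, Primary and secondary outcomes {20a}, the model is: "Fixed effects will be centre, baseline assessment for the outcome under investigation, group, time (categorical), and time × group interactions". For the random part: "Participant and therapist will be included as random intercepts". The data are also fixed: "The primary analysis will estimate treatment effects at the primary endpoint of 9 m, using all outcome data from 4 and 9 months". Results are to be reported as "adjusted mean differences in scores between the groups with 95% confidence intervals and 2-sided" p-values. No reference distribution or degrees-of-freedom method is named.

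Sample size {14} allows for "clustering in therapy arm with intraclass correlation (ICC) = 0.01 with 10 therapists over the trial period". The mean caseload is put at 12, the variation in caseload is also given as 12, and the TAU arm is taken as unclustered. The power calculation is repeated at an ICC of 0.05.

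**The concern.** ML makes no allowance for the fixed effects it estimates. With hundreds of independent participants that hardly matters, but here the therapist variance is learned from about 10 therapists. In the balanced case ML in effect divides the between-therapist sum of squares by 10. The group mean uses one degree of freedom, leaving 9. Fixed centre effects use more: with two therapists at each of five sites, within-centre contrasts supply only 10 − 5 = 5. TAU participants also inform the centre effects, so the effective number lies between 5 and 9.

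An underestimated therapist variance shrinks the standard error of the group effect. Judging that effect against a normal distribution adds to the problem, because it ignores how few therapists there are. What is at stake is the p-value and 95% interval of the primary endpoint. The rule covers all models, so it also reaches the 24-month effect and the continuous secondary outcomes.

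**Working it through.** **Inputs from Sample size {14}:** 120 analysed per arm (150 × 0.8); 10 therapists with mean caseload 12; ICC 0.01, sensitivity 0.05; SD 0.866 after baseline adjustment (correlation 0.5); effect sizes 0.4 and 0.33; alpha 0.05. **From {20a}:** 4- and 9-month outcomes, centre and baseline fixed, two random intercepts.

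**Assumptions not in the document:** a variation in cluster size of 12 is a variance (CV² = 12/144 = 0.083); two therapists per site; residual correlation of 0.6 between 4 and 9 months; complete data in the 240 analysed.

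**Step 1. The stated power.** Design effect in the therapy arm: DE = 1 + ((1 + CV²) × 12 − 1) × ICC = 1 + 12 × ICC, so 1.12 at ICC 0.01 and 1.60 at ICC 0.05.

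SE = 0.866 × √((DE + 1)/120):
- ICC 0.01: 0.866 × √(2.12/120) = 0.115
- ICC 0.05: 0.866 × √(2.60/120) = 0.127

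Satterthwaite df = (DE + 1)² / (DE²/9 + 1/119):
- ICC 0.01: 4.494/0.1478 = 30.4
- ICC 0.05: 6.76/0.2928 = 23.1

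| Scenario | Stated power | Normal | Noncentral t |
|---|---|---|---|
| Effect 0.4, ICC 0.01 | 91% | 93.5% | 92.0% |
| Effect 0.4, ICC 0.05 | 85% | 88.1% | 85.2% |
| Effect 0.33, ICC 0.01 | 80% | 81.8% | 79.3% |

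The stated figures reproduce to within about one point with the t calculation.

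**Step 2. Size of the test under the null.** The {20a} model was simulated with 15,000–20,000 trials per scenario (Monte Carlo SE 0.15–0.18 points), with equal caseloads and with caseload variance 12. The t rows use the df from step 1 (30 and 23) as a stand-in for a data-based correction.

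| Fit | Reference | ICC 0.01 | ICC 0.05 |
|---|---|---|---|
| ML | normal | 5.7–5.8% | 7.0–7.3% |
| ML | t | 4.7% | 5.5% |
| REML | normal | 4.7–4.8% | 5.3–5.8% |
| REML | t | 3.9% | 4.3% |

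Separate simulations of the same question widen the first row to 5.6–5.9% and 6.5–7.4%.

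**Step 3. Interval width.** The ratio of the ML model standard error to the true standard deviation of the estimate is 0.975–0.986 at ICC 0.01 (1–3% too small) and 0.936–0.942 at ICC 0.05 (about 6% too small).

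**Step 4. What drives it.** With centre left out of the model, ML with a normal reference gives 5.2% and 6.3%, so the fixed centre effects account for part of the excess. With very unequal caseloads (CV about 0.9) and ICC 0.05 it gives 7.8%.

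**Step 5. Power after the change.** For an effect size of 0.4, REML with the t reference gives 90.5% at ICC 0.01 and 85.4% at ICC 0.05, against the stated 91% and 85%.

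**Step 6. The stated reason.** REML is also likelihood-based and uses the same available outcomes under the same missing-at-random assumption. The rationale in {20c} therefore does not favour ML for the continuous outcomes.

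**The case against.** The strongest reply is that the excess depends on a normal reference distribution, which the article does not state and which a statistical analysis plan may settle. ML with t on the planning degrees of freedom gives 4.7% and 5.5%, so ML alone does not breach 5% at the planning ICC. This stands, and a flat claim that the primary test exceeds 5% would go too far. It does not dispose of the point, because the article does fix ML: a later plan could add degrees of freedom but could not adopt REML, or the REML-based Kenward-Roger correction, without departing from {20c}.

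At ICC 0.01 the remedy also misses 5% by more (3.9%, or 1.1 points below) than ML with a normal reference does (0.6–0.9 points above). That is true, but its miss is on the conservative side.

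Four stronger readings are tempting and not supported:
- **Sizing and analysis disagree.** The power figures sit closer to a finite-df calculation, but the article names no power method. Normal theory with the ICC applied to the unadjusted SD of 1 gives 93.1%, 85.6% and 81.1%, so the method cannot be read off the figures.
- **The participant random intercept makes the 9- and 24-month standard errors too small.** This requires the baseline correlation to decay over the visits. The quoted range of 0.4–0.7 describes previous data and is not a time trend; with equal correlations the same calculation returns 5.0%.
- **The therapist effect wrongly extends to TAU.** Section {20c} already says the random effects reflect partial nesting, and {14} plans no TAU clustering.
- **Size above 8%.** This needs an ICC of 0.10, which the protocol does not use (8.4%), or a therapist effect absent at 4 months and present at 9 months (8.2%).

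**Conclusion.** The concern holds in a limited form. The article states an estimator that biases the therapist variance downward when there are about 10 therapists and centre is fixed, and gives a reason that does not require it. With normal-based inference the nominal 5% test runs at about 5.6–5.9% at the planning ICC of 0.01, an excess of under one point. At the sensitivity ICC of 0.05 it runs at about 6.5–7.4%, with standard errors about 6% too small.

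The size rests on the normal reference, two therapists per site and the other assumptions listed. The simulations concern the primary model; the 24-month and secondary models share the mechanism but were not sized here. This is a worthwhile, cheap improvement rather than a flaw that must be corrected before the trial can be relied on.

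**What to change.** Replace the estimation sentence in {20c} with: *Linear mixed models will be fitted by REML with Satterthwaite or Kenward-Roger degrees of freedom; logistic mixed models by maximum likelihood.* The missing-at-random statement can stay as it is.

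The cost is one sentence and a software option, slightly wider intervals, and mild conservatism (about 4% size) if the therapist ICC is near 0.01. Planned power is essentially kept. Allowing the residual variance to differ by assessment time is an optional robustness step; it corrects no demonstrated error.

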### Plans to give access to the full protocol, participant-level data, and statistical code {31c}

The investigators will permit trial-related monitoring, audits, and Research Ethics Committee (REC) review by providing the Sponsors, the DMEC, and REC direct access to source data and other documents as required.

Anonymised datasets generated during and/or analysed during the current study will be available, and the corresponding statistical code, upon request post publication of the trial results from the Principal Investigator (PI), following review of appropriateness of request by the trial team.

## Oversight and monitoring

### Composition of the coordinating centre and trial steering committee {5d}

The trial has been carefully designed to ensure compliance with Good Clinical Practice and scientific integrity. The research programme development, design, and implementation will be managed by the PI and the co-applicants, in consultation with experts-by-experience consultants and other expert collaborators from within and outside of the PI’s institution. The trial will comply fully with KCTU Standard Operating Procedures. Dedicated Trial Coordinators will assist in the day-to day management of the project reporting to the PI. A Trial Management Group will meet monthly; its membership will include the investigators, the Trial Coordinators, and site leads. It will be chaired by the PI and will manage the day-to-day running of the study and ensure good communication between trial sites, receiving monthly reports from each site on recruitment, therapy completion, adverse events, reviewing progress against milestones, and finding solutions to problems as they arise. It will oversee the preparation of reports to the Trial Steering Committee (TSC) and DMEC.

The TSC will oversee the study on behalf of the trial Sponsor and Funder and ensure that the study is conducted within appropriate NHS and professional ethical guidelines. It will provide advice on all appropriate aspects of the project; will oversee progress of the trial, adherence to the protocol, participant safety, and the consideration of new information of relevance to the research question; will ensure the rights, safety, and well-being of the participants are given the most important considerations and should prevail over the interests of science and society; will ensure appropriate ethical and other approvals are obtained in line with the project plan; will agree proposals for substantial protocol amendments and provide advice to the sponsor and funder regarding approvals of such amendments. It will comprise six independent members: a chairperson, a clinician, health economist, statistician, and two experts by experience. The PI, Trial Coordinators, and Therapy Lead will join the meeting as observers.

### Composition of the data monitoring committee, its role, and reporting structure {21a}

The DMEC will monitor the following: (1) recruitment of study participants; (2) ethical issues of consent; (3) quality of data (including missing data and unblindings); (4) the incidence of serious adverse events (SAEs); (5) any other factors that might compromise the progress and satisfactory completion of the trial. The Chair will be responsible for confirming judgements on the likelihood of any SAE’s relatedness to trial procedures as well as the SAE’s intensity and unexpectedness. The DMEC will make recommendations to the TSC on whether there are any ethical or safety reasons why the trial should not continue, with the safety, rights, and well-being of participants being paramount. It will consider the need for any interim analyses, including potential requests from the Funder, and will advise the TSC regarding the release of data and/or information. The DMEC will consist of three independent members: a chairperson, a clinical academic, and a statistician. The PI, trial coordinators, and statisticians will attend parts of the DMEC meeting to provide reports but will not be members or be present when unblinded data is discussed. The DMEC charter is in the study site file and can be provided on request.

## Patient and public involvement (PPI) strategy

One of the co-applicants (EL) is an expert-by-experience researcher and will be involved at all stages of the research, from the application through research delivery to dissemination. She will be part of the Trial Management Group and will lead on the qualitative aspects of the study. In addition, we will have local PPI reference groups who will be asked to contribute to the delivery of the trial in a range of ways, e.g. consultation and piloting on assessment protocols; reviewing materials; supporting training of staff; supporting recruitment to the trial; conducting qualitative interviews with participants in the intervention group; and assisting with dissemination. Experts by experience researchers conducting the interviews will be provided with supervision from EL and site leads.

### Adverse event reporting and harms {22}

Best practice, professional guideline, and local NHS policies for monitoring mental state and risk will be followed throughout the participants’ involvement in the trial and will be facilitated by close liaison with clinical teams. The safety of the intervention will be monitored closely during therapy sessions and through regular contact with the participant’s clinical team or GP.

The occurrence of adverse events (AEs) will be monitored actively and systematically and recorded by research workers and therapists, following guidance from the CONSORT-SPI [74] with the extension for non-pharmacologic treatment, and the extension for reporting of harms. Reasons for withdrawal from the study will also be recorded. Medical Research Council Guidelines for Good Clinical Practice in Clinical Trials will also be followed to ensure good governance of the trial for integrity and participants’ safety and well-being.

To ensure active surveillance of harms, at each assessment point, research workers will actively check for the occurrence of specific AEs using a structured checklist completed with the participant. Clinical notes will additionally be checked by unblinded members of the research team for any further undisclosed record of AEs. This extra procedure is to ensure completeness of records and to address the possibility of an increased likelihood of disclosure of AEs in the TF-CBTp condition, as a result of greater frequency of contact and the therapeutic relationship.

Good Clinical Practice guidance for non-CTIMPs (Clinical Trial of an Investigational Medicinal Product) studies will be followed to make decisions regarding seriousness (i.e. AEs vs SAEs), relatedness to the trial (i.e. Related Events (REs) and serious related events (SREs), and unexpected serious related events (USREs).

AEs are defined by the Health Research Authority as any untoward medical occurrence, unintended disease or injury, or untoward clinical signs in participants, whether or not related to the treatment, which require additional support or input from health professionals. In addition, since an important subsidiary goal of the trial is to establish the safety of the intervention, issues specific to psychological therapies [103, 104], and specific concerns clinicians have about trauma-focused therapy with psychosis individuals, will also be monitored, namely clinically significant increases in mental health problems and/or risky or problematic behaviours; harm to self/others, including suicide attempts; harm from others; emergency room visits; or crises. Clinically significant increases will be operationalised as an unresolved exacerbation requiring increased involvement from the care team, e.g. requiring a change in treatment plan. Distress or complaints associated with therapy, completion of assessment measures, or any other trial procedure would also constitute AEs.

The causes for the AEs will also be recorded and monitored. For each AE, the following potential reasons will be identified: victimisation (aggressive behaviour, sexual abuse/assault, physical abuse/assault, emotional abuse/psychological maltreatment, exploitation, and other victimisation); mental health/psychological problems (excessive use of substances, general distress, psychotic symptoms, PTSD symptoms, suicidal ideation, and other psychological); trial procedures (group allocation, assessments, or therapy); physical health, including COVID-19; accidents or natural disasters; and other.

AEs will be assessed initially at three levels of severity, namely mild, moderate, and severe, which reflect the severity or impact of the event on the person at the time, and is distinct from seriousness. Seriousness relates to the outcome of the event and is the criteria for defining regulatory reporting obligations: SAEs are defined as death and life-threatening events (Category A), incidents which acutely jeopardise the health or psychological well-being of the individual, resulting in immediate hospital admission and/or persistent or significant disability or incapacity (category B), or resulting in injury requiring immediate medical attention (category C). However, in this study, any AE rated as ‘severe’ will automatically be classified as an SAE.

AEs will be categorised for severity and seriousness by the site leads/Trial Coordinators. Relatedness to the trial will be judged based on whether the event resulted from administration of any of the research or therapy procedures, according to a temporal relationship (i.e. SREs). Unexpectedness of an event to the intervention will be judged based on whether the event is unexpected or unexplained given the participant’s clinical course, previous conditions and history, and concomitant treatments (i.e. USREs).

Events identified as SAEs will be further reviewed by the PI initially and additionally by the chair of the DMEC. Only SAEs that have been judged by the PI and the chair of the DMEC to be USREs will be reported to the REC. The DMEC will be responsible for investigating further, if there are any concerns about unexpectedly high rates of SAEs, SREs, or USREs, which may include being unblinded as to trial condition or seeking further data on adverse events, and will advise the TSC on any ethical or safety reasons why the trial should be prematurely ended. The Funder will immediately be notified on receipt of any information that raises material concerns about safety or efficacy, and of any recommendations from the DMEC to end the trial.

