### Provisions for post-trial care {30}

There is no provision for post-trial care in the study, and participants will remain under the care of their usual mental health team or primary care services (if discharged from secondary care during their participation in the trial). The trial is covered by the Sponsor’s (King’s College London) indemnity insurance.

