In relation to cost-effectiveness, we will collect data on service use and health-related quality of life at all assessment time points. In addition, service use will be assessed for the previous 3 months at the ‘keeping in touch’ phone calls between the end of therapy (9 m post-randomisation) and final follow-up (24 m post-randomisation), to maximise the accuracy of these data. See ‘Economic analysis’ section for further details.

Acceptability of the therapy, through qualitative interviews, will also be assessed as a secondary outcome in the therapy group, and in therapists delivering the therapy. This qualitative element will identify key aspects of acceptability and tolerability in receiving and implementing the therapy that could not be detected by quantitative measures alone. Therapeutic alliance will also be assessed in the intervention group only (Fig. 3).

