### Participant timeline {13}

Research team members will conduct all eligibility and research assessments; all follow-up assessments will be conducted by research workers blind to study group. Therapy will last 9 m in the intervention group. Participants will remain enrolled in the study for 2 years in total.

Research assessments to assess PTSD and secondary outcomes, including cost-effectiveness outcomes, will take place at four time points (baseline, 4 m (mid-therapy), 9 m (end of therapy; primary endpoint), and 24 m (15 m post-therapy) post-randomisation). There will also be four ‘keeping in touch’ phone calls where service use will be assessed and contact details updated (at 12 m; 15 m; 18 m; and 21 m, post-randomisation). The 24 m post-randomisation assessment will enable us to determine whether therapy effects endure on both our primary and secondary outcomes. The 4 m assessment and the phone calls will help retention into the trial and reduce loss to follow-up, by avoiding having lengthy periods of time in the study without contact from the research team.

Qualitative interviews with participants in the intervention group will occur once participants have concluded or chosen to end therapy. Qualitative interviews with therapists will occur once they have completed therapy with a minimum of two participants.

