### Plans to promote participant retention and complete follow-up {18b}

A number of strategies are planned to maximise participant retention into the trial and ensure completeness of outcomes. A ± 1 m window will be allowed for completion of assessments at each time point. Assessment measures will be clearly prioritised so that the most important will be collected first to avoid missing data. The CAPS-5 [69] (primary outcome) will always be administered first, followed by the PSYRATS [67] and the health economy measures.

Participants who choose to end the therapy early or deviate from the allocation protocol (e.g. someone receiving trauma-focused therapy in the TAU group) will still be invited to complete all follow-up assessments. Participants will be remunerated for their time and travel, which secures good concordance with trial procedures, even in those who end therapy early [94]. There will be flexibility around the location of assessments, including remote assessments or home visits for participants who are unable to travel. Anyone who moves within the UK will be followed up.

A mid-therapy assessment is included to minimise attrition from the trial, as 9 m is a long period without contact with the research team for this population. This is particularly the case for the control group and those who end therapy early, and the extra assessment stage will provide data that can be used in the linear mixed model for the intention-to-treat analysis for those who drop out of the study at the primary endpoint. This adds some validation to a missing-at-random assumption for outcome missingness. The four ‘keeping in touch’ phone calls will also help to retain participants in the trial until the final assessment 24 m post-randomisation.

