### Frequency and plans for auditing trial conduct {23}

It is anticipated that the DMEC and TSC will be convened on a 6-monthly basis, but either the research team or the DMEC/TSC will have the opportunity to request an increased frequency of meetings, should it be indicated. The DMEC will receive open reports showing summary measures of the data across the sample and will be the only committee to receive closed reports displaying summary measures of the data split by treatment group.

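### Between 9 and 24 months no adverse event check with the participant is described, so events that never reach services rest on one recall of about 15 months

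*Protocol article*

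**What the plan says.** All references are to the protocol article.

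- **Checklist.** Adverse event reporting and harms {22} provides that "at each assessment point, research workers will actively check for the occurrence of specific AEs using a structured checklist completed with the participant".
- **Assessment points.** Participant timeline {13} lists them as "baseline, 4 m (mid-therapy), 9 m (end of therapy; primary endpoint), and 24 m (15 m post-therapy) post-randomisation".
- **Calls.** The same section describes four further contacts separately, as "phone calls where service use will be assessed and contact details updated (at 12 m; 15 m; 18 m; and 21 m, post-randomisation").
- **Reason for the calls.** Outcomes {12} asks about service use over the preceding 3 months at these calls "to maximise the accuracy of these data".
- **Windows.** The retention section {18b} states: "A ± 1 m window will be allowed for completion of assessments at each time point".
- **Other AE sources.** Section {22} also has unblinded staff look through clinical notes for AEs that were not disclosed, has research workers and therapists record AEs, and keeps up contact with the clinical team or GP. No interval is given for the notes check or for this contact. The oversight section {5d} has sites report AEs to the Trial Management Group each month.

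**The concern.** The participant checklist is the protocol's named tool for active surveillance of harms, and establishing safety is one of the trial's declared subsidiary goals. The schedule applies the checklist reasonably often while therapy is running, then leaves one long interval after it ends. The research team speaks to each participant four times in that interval, but the stated content of those calls does not include AEs.

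Two things are at stake. The first is completeness. Section {22} monitors harm to self and harm from others, and lists assault, emotional abuse and exploitation among the causes to be recorded. Some such events never come to the notice of any service, and participant report is then the only source. The second is dating. Relatedness is judged partly on timing, and dates recalled over more than a year are a weak basis for that judgement.

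The plan's own reasoning points the same way: it treats 3-month recall as worth four extra contacts per participant for service use, yet leaves safety events on the same calls unasked.

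**Working it through.** No power or variance calculation applies. The check is arithmetic on the stated schedule, followed by a comparison of the sources.

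**1. Inputs.** Checklist at baseline, 4, 9 and 24 months ({13}, {22}); calls at 12, 15, 18 and 21 months ({13}); window ±1 month at each assessment ({18b}); planned sample 300 ({14}).

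**2. Intervals between participant checklists.**
- Baseline to 4 months: 4 − 0 = 4 months.
- 4 to 9 months: 9 − 4 = 5 months.
- 9 to 24 months: 24 − 9 = 15 months. This agrees with the protocol's own figure of 15 months after the end of therapy.

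**3. Share of follow-up.** 15 / 24 = 62.5%. With all 300 participants retained, this is 300 × 15/12 = 375 person-years; attrition would lower it.

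**4. Effect of the windows.**
- Shortest: 9-month visit late (10), 24-month visit early (23): 23 − 10 = 13 months.
- Longest: 9-month visit early (8), 24-month visit late (25): 25 − 8 = 17 months.

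**5. If the calls carried a checklist.** Contacts at 9, 12, 15, 18, 21 and 24 months are nominally 3 months apart throughout.

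**6. What each other source adds after 9 months.**

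| Source | What it can find from 9 to 24 months |
|---|---|
| Therapist recording | Nothing from sessions, because therapy has ended |
| Clinical notes check | Events that someone wrote down; timing not stated |
| Clinical team or GP contact | Events known to them; interval not stated |
| Monthly site reports | Nothing new; they pass on events already detected |
| Service-use interview (AD-SUS) at the calls | Health and social service use for any cause, which should include admissions and emergency visits; no route to the AE record is described |

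**7. Comparison with the serious event definition.** Section {22} defines serious events mainly through death or threat to life, immediate admission, lasting disability, or injury needing prompt medical care. Most of these would leave a trace in one of the sources above. The events left to recall alone are those that reach no service. Because any AE rated severe is also classed as serious in this trial, that remainder could include some serious events, but the documents give no rate from which to count them.

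**The case against.** The strongest reply is that the checklist is one source among several. The sentence that follows it in section {22} adds the notes check, expressly for completeness. Liaison with clinical teams runs throughout participation, and the GP is named as a contact. That answers much of the worry about a participant who leaves secondary care ("if discharged from secondary care during their participation in the trial"). The article condenses a full protocol, and its schedule figure is not reproduced in the text at hand, so the call script and the timing of the notes check may be set out elsewhere. Therapy, whose safety is the stated interest, ends at 9 months, and checklists fall at 4 and 9 months. Finally, the callers are blinded, and every extra conversation about harms is a chance for allocation to be disclosed.

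Much of this stands. A reader might infer that AEs are looked for only at assessments, that the notes check happens at those same visits, or that serious events will generally surface more than a year late and miss DMEC meetings ("It is anticipated that the DMEC and TSC will be convened on a 6-monthly basis"). The documents support none of these. The notes check and the clinical contact are separate sources, the notes check has no stated timing, and most events meeting the serious definition would come to the notice of services.

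What the reply does not remove is the stated schedule. The text does not simply leave the calls undescribed: it says what they cover, keeps them apart from the assessments, and ties the checklist to the assessments. Nor does any other listed source reach an event that the participant has told nobody about. The blinding point is a real cost but a small one, because blinded workers already use the checklist at the follow-up assessments.

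**Conclusion.** The point holds in a limited form. From 9 to 24 months no AE check with the participant is described, and for events that do not reach services the record depends on a single recall of about 15 months (13 to 17 with the windows). This is a weakness in how completely later harms are ascertained. It does not show that serious events in general will be missed or delayed.

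The conclusion rests on three assumptions: that the calls contain what section {13} says they contain; that some victimisation and self-harm is not disclosed to services; and that recall worsens with the length of the interval, which is the protocol's own ground for the 3-monthly service-use questions. How many events are affected cannot be estimated from the documents. Nor do they show that the loss would differ between arms after therapy has ended, so the supportable consequence is under-counting and poor dating, not a bias in a known direction.

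The change is worth making because the contacts and most of the data are already planned.

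**What to change.** Amend Participant timeline {13} and Adverse event reporting and harms {22} in two respects.

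1. At the 12, 15, 18 and 21 month calls, give a short AE checklist limited to event types and dates, with no questions about therapy. This brings the nominal recall interval down from 15 months to 3.
2. Have unblinded staff reconcile hospital admissions and emergency visits reported on the AD-SUS, in both arms, against the AE log. This assumes that the trial's version of the AD-SUS itemises these contacts; its items are not shown.

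If the full protocol or call script already provides for either step, the article needs only a sentence saying so. The fix does not require the notes check to run on any particular cycle.

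Cost: a minor amendment, a few more minutes on four scheduled calls, a reconciliation listing from data already collected, and more events to process. Since the calls also serve retention, the checklist should stay brief. There is a small added risk that a participant reveals allocation to a blinded caller; asking about event types only, with the reminder already planned before assessments, limits it.
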